### Outcome measures

#### Primary outcome measures

Amphetamine Cessation Symptom Assessment (ACSA) is a clinician-based scale to assess withdrawal symptoms of patients with ATS addiction, which includes three subscales of “anxiety and mood,” “fatigue,” and “craving.” Items are scored on a 5-point scale ranging from 0 to 4 with higher scores representing more severe PAAS. The ACSA has been validated to be of high sensitivity, reliability, and specificity [29].

The change in ACSA scores will be measured at baseline, after the completion of treatment (week 4), and at the follow-up period (week 12, week 24, week 36, and week 48). The primary outcome in this study is the change in the ACSA between baseline (week 0) and the completion of treatment (week 4).

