### Sample size

A total of 300 participants are expected to be recruited in this study (150 allocated to receive the EA group, 150 to the waitlist group), allowing for 20% loss to follow-up. Though a sample size of 300 participants is believed to ensure internal validity, a pilot study will be performed if the condition permits, given that there are currently no literatures that reported a change of ACSA scores in PAAS patients receiving acupuncture therapy to support the calculation of sample size.

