### Statistical analysis

The statistical analysis will be conducted by independent third-party professional statisticians and will be performed using SAS (Ver9.4). All statistical analyses will follow the principle of intention-to-treat (ITT). All patients who underwent randomization will be included in the final analysis. A two-sided test at a significance level of 95% is deemed as statistically significant.

For the description of baseline features, the mean with the standard deviation or range with the minimum and maximum will be used for continuous data. For homogeneity tests of baseline characteristics between the two groups, a two-sample *t*-test will be used for continuous data. If there are baseline characteristics that exhibit statistically significant differences between the groups, analysis of covariance or logistic regression will be used for analysis and adjustment of the baseline characteristics.

A generalized linear mixed-effects model will be employed to analyze the primary outcome and other repeatedly measured outcomes. Randomization, baseline assessments, stratification factors, assessment times, and time-intervention interaction will be included in the regression models as covariates. It could be used to assess within-participant correlations due to repeated measurements, as well as between-group variations. A *p*-value of less than 0.05 will be considered to indicate statistical significance.

Compliance will be represented primarily by the number of treatment sessions attended. Participants had good compliance, with treatment of more than 80%.

For the comparison of AEs and combined use of drugs between groups, a *χ*^2^ test or Fisher’s exact test will be performed. The data for AEs will be collected from symptoms reported by the patients, and observations by a researcher.

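### The listed mixed model gives baseline one slope for all visits, which could cost precision in the week-4 primary comparison; a baseline-by-visit term removes that risk almost free

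*Protocol article*

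**What the plan says.** The primary endpoint concerns a single visit. Under Primary outcome measures: "The primary outcome in this study is the change in the ACSA between baseline (week 0) and the completion of treatment (week 4"). The scale is also scored repeatedly, "after the completion of treatment (week 4), and at the follow-up period (week 12, week 24, week 36, and week 48"), which gives five post-baseline visits. One model covers them all: "A generalized linear mixed-effects model will be employed to analyze the primary outcome and other repeatedly measured outcomes". Its terms follow in the next sentence: "Randomization, baseline assessments, stratification factors, assessment times, and time-intervention interaction will be included in the regression models as covariates".

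The list contains one interaction, time by intervention. No baseline-by-time term appears anywhere in the article, and neither the covariance structure nor the random effects are stated. The Sample size section plans 150 per arm, "allowing for 20% loss to follow-up", and gives no effect size, SD or power, with this explanation: "there are currently no literatures that reported a change of ACSA scores in PAAS patients receiving acupuncture therapy to support the calculation of sample size".

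**The concern.** An analyst who fits the listed terms lets the treatment effect differ by visit but estimates one baseline coefficient from all five visits. Four of those visits lie 8 to 44 weeks after the primary one. If baseline ACSA predicts the week-4 score better than it predicts later scores, the common coefficient need not suit week 4, and the baseline adjustment there removes less noise than it could. The confidence interval for the primary comparison would then be wider than the same data allow. The same would hold for each repeatedly measured secondary scale. With no power calculation in the article, there is no documented margin of precision to spend.

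**Working it through.** **Inputs from the article.** 300 participants at 1:1, 20% loss, five post-baseline visits, primary contrast at week 4, two-sided 5% level. The loss arithmetic is consistent: 300 × 0.80 = 240, or 120 per arm. The 300 itself cannot be derived, because no effect size, SD or power is given.

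**Inputs assumed.** All correlations, equal SDs (set to 1) and time as a categorical factor. Two covariance structures are shown because none is stated.

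**Formula.** With complete data and a separate treatment effect at each visit, the week-4 estimate under a common slope b is

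(difference in week-4 means) − b × (difference in baseline means).

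With n per arm and r4 the correlation of baseline with week 4 (equal to b4 when the SDs are 1):

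- common slope: variance = (2/n) × [(1 − r4²) + (b4 − b)²]
- week-4 slope: variance = (2/n) × (1 − r4²)
- inflation = (b4 − b)² / (1 − r4²)

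Under compound symmetry (a random intercept), b is the plain mean of the five slopes. Under an unstructured covariance it is the generalised-least-squares weighted slope. Modelling change instead of score lowers every slope by 1 and leaves b4 − b unchanged.

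**One case in full.** Slopes 0.7, 0.6, 0.5, 0.4, 0.3 have mean 0.5. Inflation = (0.7 − 0.5)² / (1 − 0.49) = 0.04 / 0.51 = 7.8%. The unstructured weighting gives b = 0.667, and the inflation is only 0.033² / 0.51 = 0.2%.

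**Range.** UN = unstructured, CS = compound symmetry. Power is at week 4, with the effect set so that visit-specific slopes give 80%.

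| Assumed slopes, week 4 to week 48 | b, UN / CS | Inflation, UN / CS | Power, UN / CS |
|---|---|---|---|
| 0.5 throughout | 0.500 / 0.500 | 0% / 0% | 80% / 80% |
| 0.6 to 0.4 | 0.533 / 0.500 | 0.7% / 1.6% | 79.7% / 79.4% |
| 0.7 to 0.3 | 0.667 / 0.500 | 0.2% / 7.8% | 79.9% / 77.0% |
| 0.7 to 0.1 | 0.914 / 0.400 | 9.0% / 17.6% | 76.5% / 73.3% |
| 0.70 to 0.17, first-order autoregressive by visit | 0.515 / 0.388 | 6.7% / 19.1% | 77.4% / 72.8% |

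The second to fourth rows assume a correlation of 0.6 between any two post-baseline visits. In the fourth row the unstructured weighting puts the common slope above the week-4 slope, so the common slope is not always too shallow.

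**Simulation with dropout.** With 300 randomised, 20% random dropout by week 48 and 600 replicates, the variance ratios (common over visit-specific; UN / CS) were 1.005 / 1.005 for a constant slope, 1.002 / 1.091 for 0.7 to 0.3, and 1.064 / 1.176 for the autoregressive case. With a constant slope, the visit-specific model cost nothing measurable.

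**Further patterns.** Correlations falling from 0.68 to 0.24 give 6.7% (UN) and 13.2% (CS). A steeper fall, 0.59 to 0.11, gives 10.6% and 15.7% by formula but 7.8% and 12.0% in a simulation at 120 per arm. That gap is unexplained, so the formula values are not used for the range.

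**Participant equivalent.** At 7%: 240 × 0.07 / 1.07 = 16 effectively lost. At 13%: 240 × 0.13 / 1.13 = 28.

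**Unequal SDs.** A slope is the correlation times the SD ratio. For correlations falling from 0.74 to 0.40, equal SDs give 3.2% (UN) and 7.7% (CS). If the SD rises from 1.0 to 1.4 by week 48, the last slope is 0.40 × 1.4 = 0.56 rather than 0.40, and the inflation drops to 0.3% and 2.0%. Falling SDs push it the other way.

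**The case against.** The strongest reply is that nothing here is invalid. A common baseline slope with a visit-by-treatment interaction is a legitimate adjusted model. The article is also a condensed account: it says which terms will be included, not that no others will be, and a fuller analysis plan could add this one. The premise of a fading slope is not in the documents either, and with an unstructured covariance the loss can be trivial even when the fade is large (0.2% for 0.7 to 0.3).

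Most of this stands. It rules out two stronger readings. A reader might infer that the primary estimate is biased or its type I error affected. The documents do not support that: treatment is randomised, and the variance is what changes. A reader might also infer that precision is certainly being lost. That would require correlations or SDs, and the article gives none.

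What does not stand is that this is merely unwritten detail. The article gives an explicit term list and names one interaction, so an analyst who follows it fits the restricted model.

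**Conclusion.** The point holds as a conditional loss of efficiency. As listed, the model applies one baseline slope to weeks 4 to 48, and the week-4 variance is inflated whenever that slope differs from the week-4 slope. On assumed correlations with equal SDs, the inflation is about 0% to 9% with an unstructured covariance and 0% to 19% with compound symmetry. At the upper ends, 80% power would become 76.5% and 72.8%. The loss is near zero if the slope is stable, smaller if SDs rise over follow-up and larger if they fall. No single figure can be given, because the article states neither the covariance structure nor any ACSA correlation. This is an inexpensive improvement and not an essential correction.

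**What to change.** In the term list of the Statistical analysis section, add a baseline-by-assessment-time interaction and state that assessment time is categorical. State that the primary estimate is the week-4 electro-acupuncture minus waitlist contrast from that model. Use the same term, with each scale's own baseline, for the repeatedly measured secondary outcomes.

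The cost is one line of wording and four extra parameters per model (five baseline slopes instead of one) with about 240 participants. It needs no new data and no further recruitment. It should be settled before the outcome data are examined.

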### Concomitant treatments

All participants could receive any other treatment during the trial. All treatments will be recorded on the CRF.

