**Participants**										
Screening	√									
Demography	√									
Informed consent	√									
Randomization		√								
Combined medication record	√	√	√	√	√	√				

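### The comparison of concomitant drug use does not define use relative to randomisation and makes no stated use of the entry medication record, so it may lose sensitivity to unequal drug changes after allocation

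*Protocol article*

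**What the plan says.** All of this is in the protocol article.

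- **Concomitant treatments:** "All participants could receive any other treatment during the trial", and "All treatments will be recorded on the CRF".
- **Participant timeline, Table 1:** the row "Combined medication record" is ticked at weeks −1, 0, 1, 2, 3 and 4. Randomisation is at week 0.
- **Statistical analysis, last paragraph:** "For the comparison of AEs and combined use of drugs between groups", the test is χ² or Fisher's exact. The text does not define the event counted as drug use, and names no covariate or stratum for this test.
- **Statistical analysis, mixed-model paragraph:** baseline assessments and stratification factors are covariates, but only in the model for the primary and other repeatedly measured outcomes.
- **Statistical analysis, population:** "All patients who underwent randomization will be included in the final analysis".
- **Sample size:** "150 allocated to receive the EA group, 150 to the waitlist group", "allowing for 20% loss to follow-up".

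**The concern.** The trial is open-label, the waitlist arm receives no electro-acupuncture until after the 48-week follow-up, and any other treatment is allowed in both arms. Waitlist patients might therefore start or increase other drugs more often than treated patients. If those drugs relieve symptoms, the week-4 ACSA difference would shrink. The χ² or Fisher test is the only analysis the article states that would show whether drug use differed by arm.

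On the ordinary reading of concomitant use, a patient on a drug at entry who stays on it is a user, even when only weeks 1–4 are counted. Such patients add between-patient variation that randomisation has already spread evenly over the arms. An unadjusted 2×2 test carries that variation in its standard error. The record that could remove it is already collected. What is at stake is the sensitivity of this check: a non-significant result could give more reassurance than it deserves.

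**Working it through.** **Inputs from the article.** 150 per arm; two-sided 5% level ("A *p*-value of less than 0.05 will be considered to indicate statistical significance"); 20% loss, so 150 × 0.8 = 120 per arm as a lower case. The article states no figure for the drug comparison, so there is none to reproduce.

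**Assumed inputs (not in the article).** b = share on a drug at entry, from 0% to 60%. Among entry non-users, s = 10% (electro-acupuncture) and 25% (waitlist) start a drug in weeks 1–4. Entry users continue.

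**Step 1: what an any-use count compares.** Proportion using = b + (1 − b)s, so the arm difference is (1 − b) × 15 points.

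- b = 20%: 28% v 40%, difference 12 points.
- b = 40%: 46% v 55%, difference 9 points. New starts over the whole arm are 0.6 × 10% = 6% v 0.6 × 25% = 15%, also 9 points.

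The any-use count therefore estimates the arm-level difference in starts without bias. The loss is in the standard error.

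**Step 2: power at b = 20%, n = 150.** Power = Φ[(d − 1.96 × SE0) / SE1], with SE0 under no difference and SE1 under the assumed difference.

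*Unadjusted.* Mean proportion 0.34, and 0.34 × 0.66 = 0.2244.
- SE0 = √(2 × 0.2244/150) = 0.0547
- SE1 = √[(0.28 × 0.72 + 0.40 × 0.60)/150] = 0.0543
- Power = Φ[(0.12 − 0.1072)/0.0543] = Φ(0.24) = 0.59

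*Conditioning on entry use.* Only the non-user stratum (weight 0.8, 120 per arm) varies. Mean start rate 0.175, and 0.175 × 0.825 = 0.1444.
- SE0 = √(2 × 0.8 × 0.1444/150) = 0.0392
- SE1 = 0.8 × √[(0.10 × 0.90 + 0.25 × 0.75)/120] = 0.0385
- Power = Φ[(0.12 − 0.0769)/0.0385] = Φ(1.12) = 0.87

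The difference is 12 points in both cases. Only the standard error changes.

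**Step 3: range of entry use, n = 150 per arm.**

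| On a drug at entry | Any use, by arm | Power, unadjusted | Power, conditioning on entry use |
|---|---|---|---|
| 0% | 10% v 25% | 0.94 | 0.94 |
| 10% | 19% v 32.5% | 0.77 | 0.91 |
| 20% | 28% v 40% | 0.59 | 0.88 |
| 40% | 46% v 55% | 0.36 | 0.77 |
| 60% | 64% v 70% | 0.20 | 0.59 |

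These powers are recomputed values. The Step 2 formula agrees to within about 0.02.

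**Step 4: sensitivity.**
- *120 per arm, b = 20%:* 0.50 unadjusted v 0.79 conditional.
- *Starts 10% v 20%, 150 per arm, b = 20%:* 0.32 v 0.58.
- *Entry users stop.* Suppose 20% of entry users stop in each arm, with b = 20% and starts 10% v 25%. Use is 0.2 × 0.8 + 0.8s = 24% v 36%.
  - Unadjusted: SE0 = √(2 × 0.30 × 0.70/150) = 0.0529; SE1 = √[(0.24 × 0.76 + 0.36 × 0.64)/150] = 0.0525; power Φ[(0.12 − 0.1037)/0.0525] = 0.62.
  - Conditional: SE0 = √[2 × (0.8 × 0.1444 + 0.2 × 0.16)/150] = 0.0443; SE1 = √[0.0385² + 0.2² × 2 × 0.16/30] = 0.0437; power Φ[(0.12 − 0.0869)/0.0437] = 0.78.
  - The gain is smaller than in Step 2, as expected.

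**Step 5: type I error.** With starts of 10% in both arms, simulation of the unadjusted test (4,000 trials each at 0%, 20% and 50% entry use) rejected in 4.3% to 5.3%. The test is valid.

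**The case against.** The strongest objection is that the article fixes only a test. A χ² on drugs started after randomisation would fit its wording equally well and would have no dilution. A condensed article commonly leaves the definition of a concomitant drug to the full protocol or SAP, which are not shown. This stands in part. A reader might infer that the plan counts pre-randomisation drugs and sets the baseline record aside, but the article says neither. What remains is that it names an unadjusted test for a variable with a collected baseline value, and gives baseline and strata adjustment only to other outcomes. The section does provide analysis of covariance or logistic regression for baseline characteristics that differ significantly, but that provision is conditional and is not assigned to drug use.

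Other points that stand:

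- **Size is unknown.** The entry criteria exclude mental disorders and severe organic disease, which could keep entry drug use low. The Background says antipsychotics are commonly used in this population, which points the other way.
- **No hidden 15-point gap.** A reader might infer that the any-use count conceals a 15-point difference. The 15 points apply to entry non-users only. At 40% entry use the arm-level difference is 9 points, and the test estimates it without bias.
- **Entry users can be informative.** They may stop, switch, add or increase drugs differently by arm. Restricting the comparison to entry non-users would miss this and would drop randomised patients, against the plan's own analysis principle.
- **Limited consequence.** Co-medication is part of what a pragmatic trial compares, and no stated decision depends on this test.

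**Conclusion.** The point holds as an inexpensive improvement to a supportive comparison. It is not an error that affects validity. The article tests concomitant drug use without adjustment, does not define use relative to randomisation, and states no role for the week −1/0 record. If continuing drugs count as use, conditioning on entry use would raise power from 0.77 to 0.91 at 10% entry use, from 0.59 to 0.88 at 20%, and from 0.20 to 0.59 at 60%.

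These figures rest on assumed starts of 10% versus 25% among entry non-users, 150 per arm, and entry users who continue. The gain shrinks if entry users stop drugs. It disappears if few take drugs at entry, or if use is already meant as drugs started after randomisation.

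A reader might go further and infer that the planned test is biased, that its false-positive rate is inflated, or that the primary result is compromised. The documents and the calculation support none of these.

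**What to change.** In the Statistical analysis section:

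1. Define the compared variable as drug use in weeks 1–4, in all randomised patients.
2. Replace the unadjusted test for drug use with one that conditions on use at weeks −1/0 and on the randomisation strata: Cochran-Mantel-Haenszel, or logistic regression with those covariates. Specify that the week 0 record is taken before allocation, since Table 1 places both at week 0.
3. Tabulate by arm the drugs started, increased and stopped after randomisation.
4. Report entry drug use as a baseline characteristic.

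The cost is a few sentences and slightly more analysis. No new visit is needed, because the record is already scheduled at weeks −1 to 4. Strata may be sparse if few patients take drugs at entry. The adverse-event comparison and the primary analysis stay as they are.

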### Discussion

ATS abuse has been increasing yearly all over the world, presenting a serious challenge to global public health [1, 36]. There are multiple reasons that could hinder the treatment of ATS addiction and even contribute to relapse in which PAAS plays a critical role. However, there are few studies focusing on this field resulting in limited treatment strategy and suboptimal clinical outcomes. Recently, acupuncture has been reported by increasing studies to be effective in treating abstinence syndrome, including both the acute withdrawal syndrome and protracted one [17, 37–39]. Therefore, we expect that this study will provide a new approach for the clinical management of ATS withdrawal. We also believe that this study will benefit patients with ATS use disorder by alleviating their protracted symptoms to facilitate their rehabilitation.

However, this study protocol has some limitations. The absence of standard treatment for PAAS makes it difficult to set a positive control in acupuncture studies. Therefore, a waitlist design is selected as the control group based on consideration of ethical consequences, which is also suitable for the pRCT design [25]. On the other hand, the broad inclusion criteria, individualized treatment, complex intervention, and patients’ expectation for acupuncture may cause multiple confounding factors to affect the results [40, 41], which cannot be totally processed through a large sample size or the regression model. Therefore, follow-up studies are needed and will be performed to further explore the potential of acupuncture therapy in this field. If it is validated to be effective in treating PAAS, it can be applied as a complementary and alternative therapy for patients and clinicians to choose.

### Trial status

The research will start in June 2021 and is expected to end in December 2023.

## Data Availability

The data set used and/or analyzed after completion of this research will be provided by the corresponding author upon reasonable request.

## Abbreviations

ATS: Amphetamine-type stimulants
pRCT: Pragmatic randomized controlled trial
PAAS: Protracted amphetamine abstinence syndrome
ACSA: Amphetamine cessation symptom assessment
VAS: Visual analog scale
HAMD: Hamilton Depression Scale
HAMA: Hamilton Anxiety Scale
MoCA: Montreal Cognitive Assessment
PSQI: Pittsburgh Sleep Quality Index
SF-36: Medical Outcomes Study 36-item Short-Form Health Survey
MDMA: Methylenedioxymethamphetamine
TCM: Traditional Chinese medicine
EA: Electro-acupuncture
AEs: Adverse events
CRF: Case report form
